**PROTOCOL SYNOPSIS**

| **Title** | **Safety and Feasibility of Allogeneic Cord Blood-Derived Cell Therapy in Preterm Infants with Severe Brain Injury** |
| --- | --- |
| **Objectives** | Primary   1. To evaluate feasibility of availability of allogeneic umbilical cord blood cells (UCBCs) in surviving preterm infants with severe brain injury. 2. To evaluate safety of administration of allogeneic UCBCs in surviving preterm infants with severe brain injury.   Secondary   - 1. To evaluate the effect of administration of allogeneic UCBCs on short and long-term clinical outcomes.   2. To evaluate the effect of administration of allogeneic UCBCs on immune responses, as measured by cytokine levels. |
| **Outcomes and outcome measures** | Primary outcomes   - 1. Feasibility: Availability of at least 4/6 HLA-matched allogeneic UCBCs sourced from the BMDI Cord Blood Bank for >60% of eligible infants.   2. Safety: Absence of serious adverse events related to UCBCs administration during and for 48 hrs post-infusion and the absence of graft versus host disease (GVHD) in the first three months after cell infusion.   Secondary outcomes   - 1. Clinical outcomes      1. Death, until 24 months of corrected age      2. Moderate to severe bronchopulmonary dysplasia, assessed at 36 weeks of postmenstrual age      3. Severe retinopathy of prematurity, assessed before discharge      4. Necrotising enterocolitis, assessed before discharge      5. Culture proven sepsis, assessed before discharge      6. Developmental delay, assessed anytime until 24 months of corrected age      7. Cerebral palsy, assessed anytime until 24 months of corrected age      8. Blindness, assessed any time until 24 months corrected age      9. Deafness, assessed any time until 24 months corrected age   2. Laboratory outcomes: Effect of allogeneic UCBCs on infant’s cytokines levels, including interleukin 1b (IL-1b), IL-6, Tumour Necrosis Factor (TNF-α), and IL-10 just before UCBC administration and 1-day and 7-day post administration |
| **Trial population** | 20 preterm infants with severe brain injury, with 10 each in each stratum (<28 weeks, ALLO-1 trial and 28-37 weeks, ALLO-2 trial), will be enrolled to receive UCBCs, if appropriate matching is achieved |
| **Description of sites enrolling participants** | This trial will only recruit participants from Monash Children’s Hospital |

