*Overview*: UCBC therapy has been investigated in clinical research for several neonatal morbidities;^4^ however, much work is still required. While autologous trials of UCBC therapy targeting neurological conditions, such as hypoxic-ischemic encephalopathy and preterm brain injury, are being investigated, research on allogeneic UCBC therapy for preterm brain injury is still preliminary. Research on allogeneic UCBC therapy is more crucial as preliminary data from the ongoing CORD-SAFE (autologous UCBC therapy in extremely preterm infants) feasibility study demonstrates that while autologous UCBC therapy may be an option for some babies, many will require a donor-sourced cell therapy as preterm birth often makes the collection of autologous UCBCs challenging.^3^ Notably, collecting UCBCs in preterm infants who deliver quickly or infants born in the context of antepartum haemorrhage and chorioamnionitis is challenging. In addition, these infants are at greater risk of severe IVH as they are likely born in poor condition, and UCBCs may not have been collected in some of these situations.

*Pros and cons of allogeneic UCB therapy*: Allogeneic UCBC therapy offers many advantages. It is readily available, can be targeted to efficacious doses, and enables repeat dosing. However, there are a few disadvantages, primarily the risk of a host-mounted immune response, which may negate the benefits due to clearance of transfused UCBCs or may carry unknown risks, which sometimes can be severe. It is unclear whether this risk in young preterm infants is similar to children and adults, as research in this group is largely lacking. In addition, HLA-matching is an important process for allogeneic cell therapy, but getting a full 6/6 match may not be feasible. On the other hand, a slight mismatch is probably desirable, as non-homologous use of allogeneic cells is not intended to engraft in the long term.

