As previously mentioned, it is not expected for cells to engraft and persist in the body in neonatal cell therapy trials.^8,13^ Preclinical studies indicate that administered cells seldom remain in the brain beyond few days to weeks.^8,13,14^ Likewise, clinical data shows that even in cases where there is a perfect 12/12 human leukocyte antigen (HLA) match, the infused cells are eliminated within approximately three months in almost all participants.^15^ Overall, the theoretical risk of GVHD from allogeneic cell therapy applications involving the use of cord blood-derived therapies in the preterm or neonatal population is highly unlikely outside of transplantation settings, as evidenced by a systematic review that found no instances of GVHD in children and adults treated with allogeneic UCB-derived total nucleated cells (TNCs) or mononuclear cell therapy.^12^

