     1. HLA matching: Allogeneic UCBCs will be obtained from BMDI Cord Blood Bank with an HLA matching of at least 4/6. As HLA matching and processing UCBCs may be time-consuming, the eligibility (neuroimaging) will be reconfirmed before administering the allogeneic UCBCs after successful HLA matching.
     2. Age of administration: Allogeneic UCBCs will be administered via IV infusion anytime from birth until three months of life, generally within 2-3 weeks of diagnosis of confirmed severe preterm brain injury.
     3. Cell infusion: Only one allogeneic UCBC infusion will be administered intravenously.
     4. UCBC dose: The infusion is aimed for 50 million total nucleated cells (TNCs) per kilogram of body weight will be administered. This therapeutic dose is based on preclinical^30^ and clinical studies^5,6^ of UCBC for different types of perinatal brain injury.
     5. Route: The UCBCs will be administered intravenously via a peripheral intravenous cannula.
  2. ***Comparison***

There will be no control group as this is a single-arm, open-label, phase-I study.

- 1. ***Outcomes***
     1. Primary outcomes
        1. Feasibility: Allogeneic UCBC therapy will be considered feasible if there is an availability of at least 4/6 HLA-matched allogeneic UCBCs sourced from the BMDI Cord Blood Bank for >60% of eligible infants.
        2. Safety: Allogeneic UCBCs will be considered as safe if there are no serious adverse events related to UCBCs during and for 48 hrs post-infusion and the absence of GVHD in the first three months after cell infusion. The safety outcomes will be reported for eligible infants where feasibility is demonstrated, and allogeneic UCBCs are administered.
     2. Secondary outcomes
        1. Clinical outcomes: The following clinical outcomes will be reported for the infants who received infusion.
           1. Death, until 24 months of corrected age
           2. Moderate to severe bronchopulmonary dysplasia, assessed as oxygen or positive pressure requirement at 36 weeks of postmenstrual age
           3. Severe retinopathy of prematurity, assessed as any retinopathy requiring anti-VEGF or laser treatment before discharge
           4. Necrotising enterocolitis, assessed as bell stage 2 or more before discharge
           5. Culture-proven sepsis, bacterial or fungal, requiring antibiotics treatment for 7 or more days before discharge

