       - Local site reaction (erythema, oedema, extravasation at site of peripheral intravenous catheter site).
       - Any sustained change of 30% or more from baseline in vital signs (HR, RR, BP, SpO2, Temperature).
     - Within the first 48 hours of infusion
       - Any event requiring cardiopulmonary resuscitation.
       - Escalation of respiratory support (intubation of an infant receiving non-invasive respiratory support; or change to high-frequency oscillatory ventilation in an infant receiving conventional ventilation at the time of UCBC infusion).
       - Fluid bolus or initiation/escalation of inotropic support.
       1. Infants will also be monitored clinically for infection within 48 hours of UCBC infusion. Appropriate tests will be performed to diagnose infection (culture-proven bacterial, fungal, viral infection, culture-negative, clinically suspected infection).
       2. Infants will be monitored for features of acute GVHD in the first three months after cell infusion, which includes
          1. Skin involvement: Any erythematous rash with or without skin peeling
          2. Gastrointestinal involvement: vomiting and diarrhoea
          3. Liver involvement: jaundice, conjugated hyperbilirubinemia, and abnormal liver function tests (LFTs).
       3. Physical examinations will be performed before the infusion. Further examinations will be performed at 1, 2, 3, 6, 9, 12, 18 and 24 months post-infusion. In the physical examinations, infants will be evaluated for features of chronic GVHD, such as

Skin involvement: rash, dryness, itching, thickening, change of colour, and temperature intolerance

Nail involvement: nail loss, brittle nails, abnormal texture

Hair involvement: loss of body or scalp hair, grey hair

Mouth involvement: dryness, sensitivity, ulcers, gum disease, tooth decay

Gastrointestinal and liver involvement: loss of appetite, nausea, vomiting, diarrhoea, abdominal distension, abdominal pain, jaundice, abnormal LFTs

Lung involvement: persistent cough, wheezing, breathing difficulties

Musculoskeletal involvement: muscle weakness and cramps, joint stiffness

Genitalia involvement: dryness, ulceration, itching, scarring, narrowing of orifices

- - - 1. The following neurodevelopmental assessments will be performed.

At term-equivalent age: General movements assessment and Hammersmith neonatal neurological examination

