**INTERVENTION (Examine**, **blood** for cytokines, **administer UCBCs)**

**Blood** for cytokines (24 h) & assess for side effects (up to 48 h)

**Blood** for chimerism (4d)

**Blood** for FBE, LFTs and chimerism (1w, 1m)

**GVHD assessment** at 2 m

**Blood** (FBE/LFTs), & **GVHD assessment** (3m)(***SAFETY***)

**MRI** at TEA

**Assessments: Neurological** (3, 12, 24 m) and **GVHD** (6, 9, 12, 18, 24m)

**Table 1**: Safety, adverse events, and neurological outcome monitoring

| Timeline | Cardiorespiratory monitoring | Infection monitoring | Physical examination | Cytokine analysis | FBE*, chimerism assessment and LFT | Neurodevelopmental assessment | Neuroimaging |
| --- | --- | --- | --- | --- | --- | --- | --- |
| -2 to 0 h | √ | √ | √ | √ |  |  |  |
| 0 to 48 h | √ | √ |  |  |  |  |  |
| 24 h |  |  | √ | √ | √ |  |  |
| 4 d |  |  |  |  | √ (Chimerism only) |  |  |
| 7 d |  |  | √ |  | √ |  |  |
| 1 m |  |  | √ |  | √ |  |  |
| 2 m |  |  | √ |  |  |  |  |
| 3 m |  |  | √ |  | √ (Chimersim is optional) | √ (TEA) | √ (MRI at TEA) |
| 6 m |  |  | √ |  |  | √ (3 m CA) |  |
| 9 m |  |  | √ |  |  |  |  |
| 12 m |  |  | √ |  |  | √ (12 m CA) |  |
| 18 m |  |  | √ |  |  |  |  |
| 24 m |  |  | √ |  |  | √ (24 m CA) |  |

**Note**: CA, corrected age; FBE, full blood examination (*-lymphocyte subset analysis for patients with abnormal FBE consistent with GVHD, and chimerism analysis will be repeated at 3, 6 or 12 months if there are detectable donor cells at 1 and/or 3 months testing); LFT, liver function test; MRI, magnetic resonance imaging; TEA, term equivalent age

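### The primary safety verdict counts related SAEs only to 48 hours and GVHD only to three months; named risks that appear later belong to no listed safety outcome and cannot qualify the word *safe*

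*Combined protocol and SAP*

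**What the plan says.** The Outcomes section (Primary outcomes, Safety) gives a decision rule in two parts, one on related SAEs and one on GVHD. Its condition for a verdict of *safe* reads "no serious adverse events related to UCBCs during and for 48 hrs post-infusion and the absence of GVHD in the first three months". The Protocol Synopsis has the same windows, beginning "Absence of serious adverse events related to UCBCs administration during and for 48 hrs post-infusion". Figure 1 places its safety label at the three-month visit.

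Other parts of the protocol look further ahead:

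- **Background (pros and cons)** gives the main disadvantages of donor cells as "primarily the risk of a host-mounted immune response, which may negate the benefits due to clearance of transfused UCBCs or may carry unknown risks", with no time limit.
- **Risk-benefit analysis** lists infection and unforeseen reactions among the other risks, also without timing. On clearance, it says that even with a perfect match "the infused cells are eliminated within approximately three months in almost all participants".
- **Safety monitoring and reporting** schedules examinations at 1, 2, 3, 6, 9, 12, 18 and 24 months: "In the physical examinations, infants will be evaluated for features of chronic GVHD, such as" changes of skin, mouth, liver and lung.
- **Table 1, note** adds that "chimerism analysis will be repeated at 3, 6 or 12 months if there are detectable donor cells at 1 and/or 3 months testing".

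The secondary outcomes include death to 24 months corrected age, and culture-proven sepsis and necrotising enterocolitis before discharge. They do not include related SAEs after 48 hours or GVHD after three months.

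**The concern.** Safety is a primary objective of this phase-I study, and the product is expected to remain in the body for longer than two days. The trial could apply its rule correctly and report the cells as safe while its own files hold a related serious event from day 4, or GVHD confirmed at six months. Such events would be known, but the protocol does not say that they must qualify the conclusion or appear beside it. Later trials would be likely to rely on the headline verdict.

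**Working it through.** The protocol gives no event rate, error level or sample-size calculation for safety, so there is no stated figure to reproduce. The check is a comparison of windows, then a short calculation.

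**1. What the rule counts**

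| Event | Counts against *safe*? |
| --- | --- |
| Anaphylaxis or other serious infusion reaction, judged related, to 48 h | Yes |
| Serious site reaction or infection, judged related, to 48 h | Yes |
| GVHD of any type, to 3 months | Yes (the rule does not restrict the type) |
| Related SAE other than GVHD, after 48 h | No |
| GVHD first found after 3 months | No |

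**2. Examinations inside and outside the GVHD window**

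Table 1 and the GVHD form in the Case Report Form each list 10 post-infusion time points: 24 h, 1 week, and 1, 2, 3, 6, 9, 12, 18 and 24 months. Five fall at or before three months. Five (6, 9, 12, 18 and 24 months) fall after it. The monitoring text leaves out the two earliest and lists 8, of which the same 5 are late.

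**3. Whether another outcome takes up the late findings**

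Death, sepsis and necrotising enterocolitis are secondary outcomes, but with no causality judgement and no link to the safety verdict. The Statistical analysis section promises a descriptive report of outcomes. Late GVHD and late related SAEs are not among the listed outcomes, so no planned analysis covers them by name.

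**4. How often the gap could matter**

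Let p be the probability that an infused infant has a late related SAE or late GVHD. The documents give no value, so p is assumed over a range. Infants are taken as independent, and no early event occurs. Then P(at least one late event) = 1 − (1 − p)^n. Here n = 20 is the planned total, and n = 10 is one stratum or a shortfall in infusions.

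| Assumed p | n = 20 | n = 10 |
| --- | --- | --- |
| 5% | 1 − 0.95^20 = 64% | 1 − 0.95^10 = 40% |
| 10% | 1 − 0.90^20 = 88% | 1 − 0.90^10 = 65% |
| 20% | 1 − 0.80^20 = 99% | 1 − 0.80^10 = 89% |

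In every cell the rule still returns *safe*, because late events do not enter it.

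**5. What a clean result supports**

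With zero counted events, the one-sided 95% upper limit is 1 − 0.05^(1/n). That is 13.9% for n = 20 and 25.9% for n = 10. Both limits apply only to events inside the two windows.

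**The case against.** Much can be said for the plan.

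*Named risks do count when they come early.* A reader might infer that the risks the protocol names cannot affect the verdict at all. The documents do not support that. Serious related reactions and infection to 48 hours, and all GVHD to three months, defeat it. Only late appearance escapes.

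*Late events are not ignored.* A reader might also infer a hole in monitoring. In fact, events after therapy are reported with no stated time limit. SAEs go to the DSMB and HREC within 7 days, and their review informs whether the trial continues. This stands. But that review governs conduct of the trial and does not alter the predefined meaning of *safe*.

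*Three months for GVHD has some support.* The Risk-benefit analysis describes clearance by about that time even after a perfect match, and this trial accepts 4/6 or better. The later chimerism tests are contingent on detecting donor cells, and do not show that persistence is expected. This also stands, although the clearance text says almost all participants, not all. It gives no support to 48 hours for other related SAEs, and no rationale for that limit is stated.

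*Extending the primary rule would be costly.* There is no control arm, and the treating physician judges causality. Under the Appendix, an event can be possibly related even where the infant's condition may have produced it. Local mortality with severe IVH is given as 43%. Under a zero-event rule that also counted late events, an assumed 5% late rate would cut the chance of a *safe* verdict from 1 to 0.95^20 = 0.36 with 20 infants. This is a sound reason not to insist on longer primary windows.

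**Conclusion.** The point holds in a limited form. As written, a related SAE after 48 hours or GVHD first found after three months cannot change the primary safety conclusion, and no listed safety outcome takes it up, although half of the Table 1 post-infusion examinations (5 of 10) come after three months. This follows from the text alone. The probabilities (64% to 99% with 20 infants for late rates of 5% to 20%) rest on assumed rates and only illustrate scale.

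Two stronger conclusions might be drawn and should not be. The first is that the primary windows must be lengthened, or the word withheld until 24 months; that is a trade-off for the investigators. The second is that 48 hours, being about 0.3% of a 24-month follow-up (2 of 730.5 days), misses nearly all the risk. That figure is a share of calendar time and says nothing about when related events occur. The severity is should-fix, not must-fix.

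**What to change.** Keep the two primary windows, or state a reason for them, the 48-hour limit in particular. Then, in the Protocol Synopsis and the Outcomes section:

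1. Replace the unqualified statement that the cells are safe with one limited to what was assessed, such as: no related SAE to 48 hours and no GVHD to three months.
2. Add two named secondary safety outcomes from data already planned: related SAEs after 48 hours, and acute or chronic GVHD to the 24-month visit. State which of the Appendix causality categories count as related, and in particular whether *possible* does.
3. Require both to be reported beside the primary result whenever a safety conclusion is drawn.

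No visit, test or treatment changes. The cost is some additional causality judgements without a control group, and a more qualified safety claim. Active infection monitoring is planned only to 48 hours, so later infections would be captured through event reporting and the sepsis outcome. The report should say so.

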Cell therapy will only be administered when preterm infants are clinically stable, which is deemed by the treating physician. Also, infants should not be receiving antimicrobial therapy for confirmed or presumed late-onset neonatal sepsis, which is active at the time of cell infusion, as their course may be unpredictable and may confound adverse events falsely attributing to the cell therapy.

- 1. ***Recruitment and identification of potential participants***

Head ultrasound or magnetic resonance imaging (MRI) scans for preterm infants admitted to the neonatal intensive care unit at Monash Children’s Hospital will be reviewed by the study team daily to identify severe brain injury. If a severe brain injury is identified on the scan, the infant’s family will be approached for consent, provided all the additional criteria are met. The eligibility will be further re-confirmed before administering the intervention.

- 1. ***Consent***

The study team will explain verbally about the trial and will also provide the Participant Information and Consent Form to the parent or legal guardian. The participant's family will be given sufficient time for consideration and family discussion for providing written, voluntary consent that is free from coercion. The team member obtaining the informed consent will also sign the informed consent form. A copy of the consent form will be given to the parent or legal guardian. Documentation about the participant’s participation and voluntary consent will be noted in the electronic medical record. Participants’ families who wish not to participate in the trial will be recorded. Similarly, eligible participants who are not approached and participants who have a severe brain injury but are otherwise ineligible will be recorded in the enrollment log.

- 1. ***Sample size***

A minimum of 20 preterm infants, with 10 each in each stratum (<28 weeks, ALLO-1 trial and 28 to 36+6 weeks, ALLO-2 trial), will be enrolled to receive UCBCs at the dose range mentioned below, if appropriate HLA matching is achieved. This sample size is consistent with other cell therapy trials in newborn infants. The number of preterm infants recruited for the safety outcome (cell infusion) may be less as some eligible infants may not suffice the criteria required for HLA matching or may not survive to receive the infusion, but the aim is to assess feasibility for at least 10 infants in each stratum.

- 1. ***Intervention details***

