**Overall outcomes during nursery stay**

| **Days of ventilation** | **Invasive** | | **Noninvasive** |
| --- | --- | --- | --- |
| **Days to room air** | **Home oxygen**  Y/N | | **Amount** |
| **Length of stay** | | **Referral to NDIS** | |
| **Term MRI brain** | | | |
| **Other morbidities or outcomes relevant to the study before discharge (please give details)**  **FEASIBILITY: Y/N HLA Matching: 4/6, 5/6, 6/6 HLA Loci matched:**  **SAFETY: Y/N**  **Necrotising enterocolitis**  **Culture proven late onset sepsis**  **Bronchopulmonary dysplasia**  **ROP**  **Intraventricular haemorrhage**  **Comments** | | | |
| **Neurodevelopment testing during admission**  **General Movements**  **HINE** | | | |
| **Medications on discharge** | | | |

| **Death before nursery discharge**  **Cause of death** |
| --- |

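### The primary safety result is limited to eligible, matched infants who are infused, when it should cover every infant in whom an infusion is started

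*Combined protocol and SAP*

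**What the plan says.** The primary safety outcome (Methods, Outcomes, Primary outcomes) sets this rule for calling the cells safe: "no serious adverse events related to UCBCs during and for 48 hrs post-infusion and the absence of GVHD in the first three months", with both periods counted from the infusion. The next sentence sets who is counted: "The safety outcomes will be reported for eligible infants where feasibility is demonstrated, and allogeneic UCBCs are administered". That is three conditions: eligible, feasibility demonstrated, and infused.

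The feasibility outcome just above it begins: "Allogeneic UCBC therapy will be considered feasible if there is an availability of at least 4/6 HLA-matched allogeneic UCBCs". The bar it then sets is a proportion above 60% among those eligible. This is the only definition of feasibility in the protocol, and it describes the cohort.

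Other places bear on who is counted:

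- **Secondary clinical outcomes, same section:** reported for all infants given the infusion, with no condition on eligibility or feasibility.
- **Protocol synopsis:** gives the same safety outcome without any restriction on who is counted.
- **Statistical analysis:** descriptive statistics, plus paired comparisons for laboratory values. No analysis sets are defined.
- **Sample size:** "A minimum of 20 preterm infants, with 10 each in each stratum". It adds that the number available for safety "may be less as some eligible infants may not suffice the criteria required for HLA matching or may not survive to receive the infusion".

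**The concern.** In a single-arm phase I study the natural safety population is everyone exposed. Here the only sentence that defines the population is narrower than that, and narrower than the population for the secondary clinical outcomes a few lines later. The extra conditions would exclude infants exposed under a deviation, for example one infused and afterwards judged not to have met the entry criteria, or one given a unit found to be below the required match.

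The number excluded may be very small, but the safety verdict fails on a single event. One omitted infant can therefore decide the primary conclusion. The match condition also bears on the outcome itself, because the risk-benefit section treats HLA matching as important in lowering GVHD risk. Eligibility can involve judgement too: uncertain injury severity is settled by discussion between clinical and radiological teams, and the study is open-label. A population that does not depend on eligibility leaves no room to question whether a classification was revisited after an event was known.

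**Working it through.** The plan gives no figure to reproduce here. The check compares the stated populations and then follows the zero-event rule through.

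**1. Who is counted, by place in the protocol**

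| Place | Infants covered |
| --- | --- |
| Primary safety (Outcomes) | Eligible, and feasibility demonstrated, and infused |
| Secondary clinical outcomes (Outcomes) | All infused |
| Safety outcome (Synopsis) | No filter stated |
| Statistical analysis | No set defined |
| DSMB and event reporting (Safety monitoring and reporting) | All events after therapy |

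The primary safety set is the narrowest of these. It can be smaller than the secondary clinical set, but never larger.

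**2. What feasibility demonstrated means for one infant**

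- The case report form has a per-infant item: "FEASIBILITY: Y/N HLA Matching: 4/6, 5/6, 6/6 HLA Loci matched".
- The study flow chart puts the feasibility label on the match step in the infant's pathway, before eligibility is re-confirmed.
- Sample size explains a smaller safety group only by individual infants lacking a match or dying before infusion.

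On this per-infant reading the condition means that a unit matched at 4/6 or better was available. The filters that remain among infused infants are eligibility and an adequate match.

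**3. Effect on the verdict**

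Let n be the number infused in a stratum. Suppose one of them is a deviating infant who has a related serious adverse event within 48 hours or GVHD within three months, and no other infant has an event.

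- All infused: 1/n events, so the rule gives not safe.
- Primary set as worded: 0/(n − 1) events, so the rule gives safe.

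The protocol does not state how many infants will be infused. It aims for at least 10 per stratum for feasibility and expects that fewer may be infused. Taking 6 to 10 as an assumed range:

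| n infused | All infused | Set as worded |
| --- | --- | --- |
| 6 | 1/6 = 16.7% | 0/5 = 0% |
| 10 | 1/10 = 10.0% | 0/9 = 0% |

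The verdict changes for any n. Only the size of the omitted rate depends on the assumption.

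**The case against.** The strongest reply is that the sentence is loose drafting with little practical effect. Eligibility is re-confirmed after matching and again on the day of infusion, and units go through pre-release testing, so deviations should be uncommon. No passage provides for re-judging eligibility afterwards or for removing infused infants. A changed verdict needs a deviation and a qualifying event in the same infant, and the documents give no basis for a probability of that. All of this stands, and it limits how often the problem would arise. It does not say how such an infant would be analysed if one occurred.

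Three stronger readings are tempting, and the documents do not support them.

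- **That the safety result disappears if availability is 60% or less.** A reader might infer this because feasibility is defined only as a cohort verdict. The sample size section, the flow chart and the case report form all use it per infant, so a cohort gate is unlikely to be intended. The chance of missing the 60% threshold is therefore not a measure of this risk.
- **That deviating infants are never counted anywhere.** Events after therapy go to the relevant parties, the DSMB reviews all adverse events, serious events reach the DSMB and the ethics committee within 7 days, and breaches go to the ethics committee. These infants also stay in the secondary clinical outcomes, including death. The gap is in the primary safety result only.
- **That an infant infused while being treated for sepsis is clearly excluded.** The protocol says "infants should not be receiving antimicrobial therapy for confirmed or presumed late-onset neonatal sepsis, which is active at the time of cell infusion", but this is a condition on when cells may be given. It is not among the listed inclusion or exclusion criteria, so such an infant could still be eligible.

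**Conclusion.** The point holds as a defect in the definition of the primary safety population. The only sentence that defines that population filters on eligibility and match, which conflicts with the all-infused set for the secondary clinical outcomes and with the unfiltered synopsis. Because the rule allows no events, one infused infant left out with a related serious event or GVHD is enough to change not safe to safe. That infant would be an observed rate of 10% to 17% if 10 down to 6 infants per stratum are infused.

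The conclusion rests on two things: that the sentence is applied as written, and that at least one infant is infused under an eligibility or match deviation. The second should be uncommon, and the documents give no rate for it. There is no numerical error in the plan, and safety oversight during the trial is not affected.

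The double use of feasibility, as a cohort verdict and as a per-infant status, is a secondary wording point. It leaves the sentence open to misreading and can be cleared up in the same edit.

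**What to change.** Replace the sentence on safety reporting under Primary outcomes with:

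> *Safety outcomes will be reported for every infant in whom an allogeneic UCBC infusion is started, regardless of HLA match, eligibility on later review, amount received, or the overall feasibility result.*

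Add that infants infused with an eligibility or match deviation will also be listed separately, with their events, so that readers can see their contribution. Use a separate term, such as matched unit available, for the per-infant status in the flow chart and case report form, and keep feasibility for the cohort verdict.

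This takes a few lines of protocol text, which as an amendment needs ethics committee approval. It needs no new data and changes no dose or clinical rule. The downside is that an event in a deviating infant now counts, so the safety result may be slightly less favourable.
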